### Recruitment {15}

All patients with aSAH at the study site will be screened for inclusion into the study. If a patient appears to be eligible for the trial, written informed consent by the patient or by his or her legal representative will be sought. Otherwise, no specific recruitment strategies are possible in this trial involving emergency patients.

## Assignment of interventions: allocation

### Sequence generation {16a}

Randomization will be performed at a ratio of 1:1. The randomization code will be generated using the electronic, web-based tool randomizer.at (https://randomizer.at/). Block randomization will be performed. The block length will be documented separately and will not be disclosed to the site.

### Concealment mechanism {16b}

Randomization using the above mentioned service is performed immediately before carrying out the trial intervention and only after all screening assessments have been performed. The service will not release any randomization information before this time, thus ensuring adequate allocation concealment.

### Implementation {16c}

An authorized investigator will randomize any given trial patient by logging on to randomizer.at immediately before carrying out the trial intervention (control vs. experimental treatment). The treatment arm assigned to the patient will be displayed instantly on the screen and sent by e-mail in addition.

## Assignment of interventions: blinding

### Who will be blinded {17a}

Not applicable, as this is an open-label trial.

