### Trial design {8}

This is a mono-center, randomized, controlled, parallel-group, open-label phase II trial. Fifty-four patients will be randomized at a ratio of 1:1 to receive either standard of care or standard of care plus the IT (Fig. 1).

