### Outcomes {12}

The primary endpoint is the proportion of subjects with a favorable outcome as measured on the Modified Rankin Scale (mRS) at 6 months after aSAH, assessed by an independent physician. mRS will be analyzed in a dichotomized fashion:
Favorable, defined as mRS 0–3 (independent)Unfavorable, defined as mRS 4–6 (dependent/dead)

Secondary endpoints are provided in Table 1.

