### Sample size {14}

The sample size calculation is based on the primary endpoint dichotomized mRS (mRS > 3) with an expected proportion of 50% in the standard-of-care group and 15% in the experimental treatment group. These assumptions are based on the first results of individual off-label treatments with the new procedure as described by [name] et al. [17, 19].

The study is planned to detect a difference between the experimental and control groups with respect to dichotomized mRS (mRS > 3) with a power of 80% using the two-sided *χ*^2^ test at a two-sided significance level of 5%. The null hypothesis is rejected if the asymptotic two-sided 95% confidence interval for the odds ratio (control vs. experimental) does not contain one. Under these assumptions, 54 patients are required for analysis.

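### No masking is provided for the physician who scores the primary 6-month mRS, because blinding is dismissed as inapplicable to an open-label trial

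*Protocol article*

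**What the plan says.** All references are to the protocol article.

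- *Trial design {8}*: "This is a mono-center, randomized, controlled, parallel-group, open-label phase II trial".
- *Outcomes {12}*: the main measure is the share of patients whose mRS is favourable "at 6 months after aSAH, assessed by an independent physician". Scores 0–3 count as favourable and 4–6 as unfavourable, with death in the unfavourable group.
- *Who will be blinded {17a}*: "Not applicable, as this is an open-label trial". The unblinding item {17b} gives the same answer.
- *Plans for assessment and collection of outcomes {18a}*: refers to Additional File 1 (not shown) for the study instruments. It says nothing on masking.
- *Implementation {16c}*: the allocated arm appears on screen and is sent by e-mail to the randomizing investigator.
- *Background and rationale {6a}*: the centre introduced the stereotactic access method and first used it in 20 of its own patients. *Sample size {14}* takes its effect assumption from those early off-label treatments.

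**The concern.** The answer under {17a} treats open-label delivery as settling the whole blinding question. It settles it for surgeons and intensive-care staff, who cannot be masked to a stereotactic catheter and days of lavage. It does not settle it for a separate physician who sees the patient at 6 months.

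The word independent in {12} does not fill the gap. It describes the rater's role, and it is not defined there. A physician with no part in the patient's care may still know the arm from the notes, the imaging, or the patient or family.

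In survivors, mRS 3 versus 4 is a functional judgement, and the whole primary analysis rests on that one boundary. With 27 patients per arm, one patient is 1/27 = 3.7 percentage points. If knowledge of the arm moves ratings, the planned logistic regression, the multiple imputation of missing values and the per-protocol sensitivity analysis cannot undo it, because all of them take the recorded score as correct.

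**Working it through.** **1. The plan's own figure.** *Sample size {14}* plans "with an expected proportion of 50% in the standard-of-care group and 15% in the experimental treatment group" for mRS > 3, with 80% power and a two-sided 5% level. For the uncorrected χ² test, with mean proportion (0.50 + 0.15)/2 = 0.325:

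n per arm = [1.96·√(2·0.325·0.675) + 0.8416·√(0.50·0.50 + 0.15·0.85)]² / 0.35² = (1.298 + 0.517)² / 0.1225 = 26.9, rounded up to 27.

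This gives 54 in total, as stated, with power 80.2%. Masking the rater changes none of these inputs.

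**2. Inputs to the illustration.**

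- From the plan: 27 per arm; the 50% control rate; the decision rule in {14} and {20a}, which rejects if the asymptotic 95% confidence interval for the odds ratio excludes 1.
- Assumed: no true effect, so 50% unfavourable in both arms (13.5 of 27 expected).
- Assumed: on average k patients on the investigational treatment (IT) who are truly unfavourable are recorded as favourable. The documents give no value for k, so a range is shown.

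**3. Formula.** Let a be the number recorded unfavourable among controls and b the number among IT patients. The Wald statistic is

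z = [ln(a/(27−a)) − ln(b/(27−b))] / √(1/a + 1/(27−a) + 1/b + 1/(27−b)),

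and the null is rejected if |z| > 1.96. The rejection rate is the sum of Bin(a; 27, 0.50) × Bin(b; 27, p) over all rejecting pairs (a, b), with p = (13.5 − k)/27. Tables with an empty cell count as not rejected.

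**4. Results (exact enumeration).**

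| k, mean IT patients shifted | Recorded IT unfavourable rate p | Share of truly unfavourable IT patients, k/13.5 | Two-sided rejection rate |
|---|---|---|---|
| 0 | 0.500 | 0% | 4.1% |
| 1 | 0.463 | 7% | 4.8% |
| 2 | 0.426 | 15% | 7.1% |
| 3 | 0.389 | 22% | 11.1% |
| 4 | 0.352 | 30% | 17.1% |

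With no shift, half of the 4.1% lies in each direction. As k grows, almost all of it lies on the side that favours the IT: at k = 3 the unfavourable-to-IT tail is 0.2%.

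**5. How close a single result can be.** With 14 unfavourable controls, 7 unfavourable IT patients give z = 1.124/0.584 = 1.92, which is not significant. Six give z = 1.327/0.602 = 2.20, which is significant. One rating decides the trial in that case.

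**6. Deaths.** mRS 6 is not open to judgement, so any shift must come from survivors scored 4 or 5. The documents give no death rate. If a third to a half of unfavourable outcomes were deaths (an assumption), 9 down to 6.75 of the 13.5 would be survivors. Then k = 1 means misrating 11–15% of them, and k = 3 means 33–44%.

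**The case against.** The strongest reply is that the plan is open-label phase II and already separates the primary rater in some way, and that nowhere does it say this physician knows the arm. A reader might infer that the endpoint is rated with knowledge of allocation. The documents do not support that: they make no provision either way for the rater, and Additional File 1, which describes the instruments, is not shown. A reader might also take the rater to be independent of the trial altogether. The phrase about not being involved in the trial stands only in the consent section {26a}, for the physician present when presumed will is determined, and not in {12}. Both points stand and limit the claim to a missing safeguard. They do not remove it, because the article answers {17a} itself and on a ground that does not hold for outcome raters.

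The size of the bias is also open to challenge. One or two shifted patients move the rejection rate only to 4.8% or 7.1%. The larger figures need a substantial share of severely disabled survivors to be misrated, more so once deaths are set aside. This stands, and it is why the result is given as a range.

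Masking may leak. An external ventricular drain is routine in both arms, so a scar from it does not identify the arm. But the IT arm has a further catheter and up to about three weeks of lavage, and patients and relatives know what was done. This too stands: masking would be imperfect, which argues for recording failures rather than for not trying.

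Finally, one might extend the criticism to the MRI and delayed cerebral infarction assessments. The article does not describe how these are read, they are secondary and analysed descriptively, and such detail commonly sits in the full protocol. They are not part of this point.

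**Conclusion.** The point holds as a missing safeguard on the sole confirmatory endpoint. The protocol declares blinding inapplicable for a reason that does not reach the outcome rater, and as written nothing prevents the mRS from being scored with the arm known. It does not establish that this will happen, nor how large any bias would be.

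If there were no true effect and ratings shifted in favour of the IT, the two-sided rejection rate would rise from 4.1% to between 4.8% (one patient on average) and 17.1% (four). This rests on 50% unfavourable in both arms, 27 per arm, the Wald rule, and a shift in the IT arm only.

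If the rater is in fact to be masked, {17a} is simply misstated and a sentence corrects it. Either way the text should change. It ranks as a cheap improvement.

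**What to change.** In *Outcomes {12}* and *Who will be blinded {17a}*, replace the blanket answer with a statement along these lines: treatment is open-label; the physician who scores the primary 6-month mRS is masked to allocation, has no access to treatment records or imaging, and patients and relatives are asked beforehand not to disclose the treatment; any unmasking is recorded for each patient.

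Cost: some coordination at the 6-month visit, and masking that will fail in some patients. No extra assessor should be needed, since a separate rater is already planned, though the documents do not cost this. The sample size stays at 54 and the analysis is unchanged.

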### Procedure for unblinding if needed {17b}

Not applicable, as this is an open-label trial.

## Data collection and management

### Plans for assessment and collection of outcomes {18a}

A description and explanation of study instruments can be found within the comprehensive flowchart in Additional File 1.

### Plans to promote participant retention and complete follow-up {18b}

No specific plans to promote participant retention are implemented in this trial. As this is a trial involving intensive care patients, participant retention is usually not an issue in the treatment phase. In surviving patients, the experience with achieving follow-up for at least 6 months is also very good.

### Data management {19}

A professional and validated data management system that is compliant with Good Clinical Practice (GCP) will be used. Details on the data management system and on measures to promote data quality are provided in Table 5.

**Table 5 Tab5:** Data management system

**General and technical features**	• Name: RDE-LIGHT version 1.5 • Compliance with good clinical practice (ICH E6 GCP) • Presence of an audit trail • Proprietary remote data entry system based on HTML forms • Developed, validated and maintained by the Clinical Trials Unit, Medical Center, University of Freiburg
**Additional documents to be created for more detailed documentation**	• Data management plan for details on procedures, responsibilities, etc. • Database plan for the description of technical specifications of the database and the e-forms (variable names, attributes, and data entry checks) • Data validation plan • Data management report for documentation of performance of data management and deviations from the data management plan, if any
**Additional measures to promote data quality and integrity**	• Programming of range checks for entered values at the CRF level • Validation of the trial database and edit checks of the e-forms before any data entry is performed • Documented training of any data entry personnel before access to the trial database is given • Review of the data for completeness, consistency, and plausibility using the SAS software. The checks to be programmed will be specified beforehand in the data validation plan. • Implementation of a query management, i.e., after running the check programs, the resulting queries will be sent to the investigator for correction or verification of the documented data • Validation of all programs that can be used to influence the data or data quality (e.g., data validation programs, programs for CRF/query tracking, programs for import of RDE-LIGHT data into SAS or for import of external data) • Source data verification (SDV) checks by the clinical research associate (100% SDV checks for critical data points)

### Confidentiality {27}

Information about trial patients will be kept confidential and will be managed under the applicable laws and data protection legislation. The data collected during the study will be collected, stored, and evaluated in pseudonymized form only, i.e., every trial participant is assigned a study-specific pseudonymous identification code. Only authorized trial personnel at the trial site have access to confidential information by which the identity of a patient can be revealed. The data collection system uses built-in security features to prevent unauthorized access to confidential participant information.

### Plans for collection, laboratory evaluation, and storage of biological specimens for genetic or molecular analysis in this trial/future use {33}

Blood samples will be retained and stored in a secure place at the trial site for future analyses of potential systemic effects of aSAH therapy. Specifically for this purpose, a local biobank will be established at the trial site. To this end, three blood samples per patient (approx. 20 ml each) will be collected along with the other trial-related blood drawings on day 2 ± 2, day 7, and day 14. The samples will be stored at − 80 °C and will be destroyed after 10 years. Institutional guidelines for the maintenance, use, and destruction of samples will be adhered to. In case specific analyses are to be performed from these samples, this will be done in separate research projects for which a separate approval from the responsible ethics committee will be requested.

## Statistical methods

### Statistical methods for primary and secondary outcomes {20a}

The effects of the experimental vs. control intervention with respect to the primary endpoint will be estimated in the intention-to-treat (ITT) population by logistic regression. As an estimate of the effect size, the odds ratio will be given with a corresponding asymptotic two-sided 95% confidence interval. The two-sided test on the difference between the two trial arms at significance level 5% will be based on the corresponding asymptotic two-sided 95% confidence interval from the logistic regression model. Data should be collected regardless of the patient’s adherence to the protocol, especially on the clinical outcome, to obtain the best approximation to the full analysis set. Data should also be collected on other therapies received post-dropout. Specifically, full details of the type of additional (non-randomized) therapy given, including when and for how long it was used and at what dose, should be collected. In case of missing values for the primary endpoint, this will be handled by multiple imputation [20].

Secondary endpoints will be analyzed descriptively using regression models. Treatment effects will be calculated with two-sided 95% confidence intervals. Details will be specified in the statistical analysis plan (SAP) which will be finalized after the end of the recruitment period, but before the start of the final analysis.

Safety analyses will be performed in the safety set including all patients for whom one of the treatments was started. All safety parameters (e.g., adverse events, laboratory assessments) will be listed by the patient and displayed in summary tables. The adverse events (AEs) are displayed in summary tables by treatment as follows.

The total number of AEs; the minimum, maximum, and mean number of AEs per patient; the total number of follow-up days (number of days in the observation period); the number of AEs per FU-day; the number of patients who had at least one AE; and the number of patients who stopped treatment due to AE will be given.

The incidence of AEs defined by the preferred term (PT) according to MedDRA will be calculated as the number of patients who experienced at least one AE with the respective PT in the percentage of the total number of patients in the safety population. In the incidence tables, the PTs will be grouped by system organ class (SOC) according to MedDRA. Additionally, the incidence of AEs defined by SOC will be calculated as the number of patients who experienced at least one AE in the respective SOC as a percentage of the total number of patients in the safety population.

Each table will be produced for the following AE sets: all AEs, AEs being at least severe, serious adverse events (SAEs), SAEs leading to death, AEs possibly related to IMP, AEs possibly related to IMP being at least severe (toxicity), SAEs possibly related to IMP, and SAEs possibly related to IMP leading to death. Incidences of AEs will be calculated with 95% confidence intervals.

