### Objectives {7}

The primary objective of this trial is to assess whether sequential cisternal lavage with urokinase, nimodipine, and Ringer’s solution administered via a stereotactically implanted catheter into the basal cisterns (investigational treatment (IT)) improves neurological outcome in patients with aSAH compared to standard treatment, as measured by the Modified Rankin Scale (mRS).

Key secondary objectives include the assessment of the effect of the IT on rates of DCI and related complications, its effect on further clinical and surrogate endpoints, and its safety. Table 1 presents the secondary objectives and endpoints in detail.

**Table 1 Tab1:** Secondary objectives and endpoints

Secondary objectives	Secondary endpoints
To assess the effect of the IT on neuropsychological outcome	**Neuropsychological outcome** at 6 months following aSAH: - Cognitive performance (Montreal Cognitive Assessment) - Health-related quality of life (SF-36) - Fatigue, anxiety, and depressive symptoms (Frontal Systems Behavior Scale, Multidimensional Assessment of Fatigue, Hospital Anxiety and Depression Scale) - Post-traumatic stress disorder (Impact of Event Scale–R) Return-to-work parameters at 6 months
To assess the effect of the IT on DCI	Rate and severity of **DCI** according to the Vergouwen criteria
To assess the effect of the IT on **delayed ischemic neurological deficits (DIND)** after aSAH	Rate of delayed ischemic neurological deficit (DIND), defined as **clinical deterioration caused by delayed cerebral ischemia (i.e., a new focal neurological deficit or decline on the Glasgow Coma Scale of 1 point not attributable to other causes)** on days 3–21
To assess the effect of the IT on the development of post-hemorrhagic hydrocephalus	Rates of shunt-dependent **hydrocephalus** at 6 months following aSAH
To assess the effect of the IT on sonographic vasospasm	**Delta mean flow velocities** of both middle cerebral arteries—measured by transcranial Doppler ultrasonography on days 3–21
To assess the effect of the IT on the need for endovascular interventions for the treatment of cerebral vasospasm	Rate of **endovascular interventions** for the treatment of cerebral vasospasm
To assess the effect of the IT on the course of intensive care therapy	**Key parameters of intensive care medicine (Sequential Organ Failure Score)**
To assess the effect of the IT on **morphological brain damage**	**Morphological brain damage** at 6 months after aSAH as assessed by MRI

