### Adverse event reporting and harms {22}

An adverse event (AE) is any untoward medical occurrence in a patient administered any dose of a pharmaceutical product which does not necessarily have a causal relationship with the use of the product. An AE can therefore be any unfavorable and unintended sign (including an abnormal laboratory finding), symptom, or disease temporally associated with the use of an IMP, whether or not related to the product.

In order to monitor the conditions of the patients from the time the patients receive the catheter implantation, the investigator is requested to report any untoward clinical event on the AE page of the CRF. Irrespective of any causal relationship, all AEs spontaneously reported by the patient or observed by the investigator will be documented in the case report form starting from randomization until the end of the study (month 6).

All AEs must be described by diagnosis or, if an underlying diagnosis is not known, by symptoms or medically significant laboratory or instrumental abnormalities. Symptoms, medically significant laboratory, or instrumental (e.g., electrocardiographic) abnormalities of a pre-existing disease are not considered an AE. Occurrences of new symptoms or laboratory or instrumental abnormalities, as well as worsening of pre-existing ones, are considered AEs. All AEs, no matter how intense, are to be followed up by the investigator in accordance with ICH-GCP until resolved or judged no longer clinically relevant or, in case of a chronic condition, until it is fully characterized.

For any AE, the following will be documented:
Characterization of the event (diagnosis; if not available, symptoms)Onset/end dateSeverity according to the common classification: (1) mild, (2) moderate, (3) severe, (4) life-threatening/disabling, and (5) deathRelationship to the IMP(s) (related/not related) or to study-specific procedures (such as stereotactic surgery or intrathecal lavage)Serious/non-seriousAction taken with IMP(s)Outcome

In this clinical trial, the following adverse events will be pre-specified (e.g., as a drop-down menu) for documentation in the CRF:
Delayed ischemic neurological deficit (DIND)DCIHydrocephalus requiring shunt implantationEndovascular interventions for the treatment of cerebral vasospasmComplications after aneurysm securingIntracerebral hemorrhageRe-SAHIntracerebral infection (meningitis and/or encephalitis)Episodes of critically increased ICP

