During each visit, it will be actively evaluated whether one of these events occurred since the last study visit.

Serious adverse events (SAEs) are subject to additional documentation and expedited reporting requirements as given by German legislation. An SAE is defined as any untoward medical occurrence that results in one or more of the following outcomes:
DeathLife-threatening situation (patient is at immediate risk of death), inpatient hospitalization, or prolongation of existing hospitalization (excluding those for study therapy and/or assessments, placement of an indwelling catheter, social/convenience admissions, respite care, elective or pre-planned treatment/surgery)Persistent or significant disability/incapacityCongenital anomaly/birth defectOther medically important conditions: conditions which, in the investigator’s opinion, may not be immediately life-threatening or result in hospitalization but may jeopardize the patient’s safety or may require intervention to prevent one of the other outcomes listed in the definition above, may also be considered serious. Examples of such conditions include allergic bronchospasm requiring treatment in an emergency room or at home, unexpected convulsions (i.e. convulsions which cannot be explained by the underlying illness) that do not result in hospitalization, development of IMP dependency or drug abuse, and suspected transmission of infectious agents by a medicinal product

In sum, established guidelines and definitions, standard operating procedures, and applicable laws and regulations will be followed in the documentation and reporting of adverse events. The results of the safety analyses described above will be reported in trial publications.

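### The all-AE, severe-AE and SAE summaries pool four of the trial's own efficacy events with treatment harms, so a benefit on those events can offset other harms in these summaries

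*Protocol article*

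**What the plan says.** All references are to the protocol article.

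- **AE summaries ({20a}).** Displayed by treatment: "The total number of AEs; the minimum, maximum, and mean number of AEs per patient", the number of AEs per follow-up day, and the number of patients with at least one AE. Incidences by MedDRA preferred term and by system organ class (SOC) follow, with 95% confidence intervals.
- **AE sets ({20a}).** "Each table will be produced for the following AE sets: all AEs, AEs being at least severe, serious adverse events (SAEs"), then SAEs leading to death and four sets restricted to events possibly related to the IMP.
- **What counts as an AE ({22}).** "In this clinical trial, the following adverse events will be pre-specified (e.g., as a drop-down menu) for documentation in the CRF". The list puts DIND, DCI, hydrocephalus requiring a shunt and endovascular treatment of vasospasm next to intracerebral hemorrhage, re-bleeding, intracerebral infection and critically raised ICP. At each visit "it will be actively evaluated whether one of these events occurred since the last study visit".
- **Efficacy endpoints ({7}, Table 1).** The same four events serve secondary efficacy objectives: "To assess the effect of the IT on DCI", "To assess the effect of the IT on the development of post-hemorrhagic hydrocephalus", "To assess the effect of the IT on the need for endovascular interventions for the treatment of cerebral vasospasm", and a separate row for DIND.

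No section takes the four events out of the AE or SAE summaries or shows those summaries both ways.

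**The concern.** The four events are ones the IT is meant to prevent. If it does, the IT arm records fewer AEs whatever happens with harm from the stereotactic operation, the lavage or the fibrinolytic. The pooled figures thus add benefit and harm with opposite signs: total AEs, mean per patient, AEs per follow-up day, patients with any AE, and the same figures in the severe and serious sets.

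This matters because safety is a stated objective and the IT adds brain surgery and intrathecal urokinase to standard care. A reader of the totals could conclude that the IT produces no more adverse events than control when an excess of other harms has been offset by fewer vasospasm complications.

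**Working it through.** **Inputs from the documents.** 54 patients randomised 1:1, so 27 per arm ({8}); the four overlapping events ({22} and Table 1); the list of summaries and sets ({20a}). The documents give no AE or SAE rates and state no safety figure to reproduce. Every rate below is an assumption.

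**1. Total AEs, one scenario.** Assume:
- four endpoint events at 30% each in control: 4 × 0.30 = 1.2 AEs per patient, halved by the IT to 0.6;
- 3 other AEs per patient in both arms;
- 0.5 additional harms per IT patient.

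| | Control | IT | Ratio IT/control |
|---|---|---|---|
| All AEs per patient | 3 + 1.2 = 4.2 | 3 + 0.5 + 0.6 = 4.1 | 0.98 |
| Without the four events | 3.0 | 3.5 | 1.17 |

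With Poisson counts over 27 patients per arm, the probability that the IT total is no higher than the control total is:
- 0.58 for all AEs (means 27 × 4.1 = 110.7 and 27 × 4.2 = 113.4);
- 0.16 without the four events (means 27 × 3.5 = 94.5 and 27 × 3.0 = 81).

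**2. Range.** Pooled ratio = (3.5 + e(1 − r)) / (3 + e), where e is endpoint AEs per control patient and r the proportional reduction by the IT. The ratio without the four events stays at 1.17.
- e = 0.8, r = 30%: 4.06 / 3.80 = 1.07
- e = 1.6, r = 70%: 3.98 / 4.60 = 0.87

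**3. Events offset per arm.** Offset = 27 × (control rate − IT rate) × number of event types affected (1 to 4).
- 50% vs 15% (borrowed from the mRS assumption in {14}, which is not an AE rate): 9.4 to 37.8 events
- 40% vs 20%: 5.4 to 21.6
- 30% vs 20%: 2.7 to 10.8

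An equal number of extra harms in the IT arm would leave its AE total level with control.

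**4. Patients with at least one SAE.** Take one endpoint event type that is serious, with rates p_C and p_T, independent of other serious harms with rates h_C and h_T. The arms show equal proportions when

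h_T = 1 − (1 − p_C)(1 − h_C) / (1 − p_T).

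| p_C vs p_T | h_C = 10% | h_C = 20% | h_C = 30% |
|---|---|---|---|
| 50% vs 15% | 47% (×4.7) | 53% (×2.6) | 59% (×2.0) |
| 40% vs 20% | 33% (×3.2) | 40% (×2.0) | 48% (×1.6) |
| 30% vs 20% | 21% (×2.1) | 30% (×1.5) | 39% (×1.3) |

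So the any-SAE proportions can look equal while true IT harm is 1.3 to 4.7 times control harm. Without the endpoint event the contrast reappears: 2.7 vs 12.7 patients of 27 in the top left cell, 8.1 vs 10.5 in the bottom right.

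**The case against.** The strongest reply is that nothing is hidden in the safety analysis as a whole, and this stands. Hemorrhage, infection and raised ICP are pre-specified, actively sought, and tabulated by preferred term and arm with confidence intervals. The four endpoint events are analysed individually as secondary endpoints. Per-patient listings are planned, so anyone holding them could derive the reduced totals. No test, margin or decision rests on the pooled totals, and Table 1 defines the safety endpoint as events related to the IT. A reader might infer that the plan conceals treatment harm; the documents do not support that. The masking is confined to the pooled summaries and possibly to SOC rows that mix the two kinds of event.

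Three further limits also stand:
- A reader might infer that any benefit lowers the totals. Only benefit on these four events does. Longer survival lengthens follow-up and can raise counts.
- That these events are SAEs is an inference from the seriousness criteria in {22} (prolonged hospitalisation, disability). The article does not say so.
- One vasospasm episode could be entered as DIND, DCI and an endovascular intervention, but the article does not say that it will be. It asks for AEs to be described by diagnosis, with symptoms only where no diagnosis is known.

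The effect of the change should not be oversold. In the scenario above, the comparison without the four events is 94.5 against 81, a difference of 13.5 / √175.5, or about one standard error. The reduced totals would remove the offset but would not establish an excess in a trial of this size.

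What does not stand is that the IMP-related sets already solve the problem. Control patients receive no IMP, so those sets give no between-arm contrast. Relation to the stereotactic procedure or lavage is recorded in {22}, but no listed AE set uses it. Preferred-term rows cannot be added up to a per-patient or any-AE figure, because patients overlap. The unseen SAP may add the split, but the AE sets are listed explicitly in {20a} and none makes it.

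**Conclusion.** The point holds for the pooled summaries and no further. The all-AE, severe-AE and, where these events are serious, SAE figures mix four efficacy events with harms, so a benefit on those events lowers the IT arm's figures and can offset other harms in them.

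The size rests wholly on assumed rates: pooled ratios of 1.07 to 0.87 against 1.17 without the four events, or equal any-SAE proportions with true harm 1.3 to 4.7 times control. The second range also assumes independence between endpoint events and other harms. With a small effect on the four events, the pooled ratio still points to harm.

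This is a cheap improvement to reporting. It does not show that the planned safety analysis fails to detect harm.

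**What to change.** In {20a} or the SAP, which is to be finalised only after recruitment ends:

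1. Keep every all-AE table as planned.
2. For the all-AE, severe-AE and SAE sets, add the same totals, per-patient, per-follow-up-day, at-least-one-event and SOC figures excluding DIND, DCI, hydrocephalus requiring a shunt and endovascular treatment of vasospasm.
3. Show the four events beside these figures, by arm.
4. State that both versions are read together, and that the pooled totals alone will not support a conclusion that the IT causes no more adverse events than control.

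The cost is a few sentences and an extra column or table for three AE sets. The four events have their own CRF entries, so no new data are needed.

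The downside is that an infarct, deficit or hydrocephalus caused by the IT itself leaves the reduced version. That version therefore supplements the all-AE version and must not be the sole basis of the between-arm comparison. No rule for merging AEs of one episode is proposed, since it would add judgement in an open-label trial.
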